**Figure 6. F6:**
[figure not shown]
Primary outcome – formation of habitual hourly walking. (A) No habitual hourly walking, and (B) Habitual hourly walking. Example of Fitbit step counts for a participant who did not achieve habit formation (A) and a participant who did achieve habit formation (B).

### Secondary Outcomes and Analysis

One of the secondary hypotheses of this trial is whether the binary outcome described above of habit formation is associated with positive changes in behavioral automaticity using the SRBAI. Behavioral automaticity is the hypothesized key MoBC for this trial. A Fisher exact test (5%, 2-sided) will be used to examine whether an hourly walking habit formation will be associated with positive changes in behavioral automaticity. Specifically, for each participant, the difference between average behavioral automaticity during the last 2 weeks of intervention and average baseline behavioral automaticity will be calculated; a positive change is defined as a difference of greater than zero. Additionally, we will model the association between habit and continuous changes in automaticity over time using autoregressive models of order 1 to account for serial autocorrelation between repeated measures of the SRBAI. Finally, a mixed-effects logistic regression will be used to assess the effects of behavioral automaticity on the development of a daily walking habit, with adjustment for other factors, such as caregiver demographic characteristics and factors related to caregiving. For this model, we will examine the fixed effects of automaticity, time, and the time-by-automaticity interaction effect to examine whether changes in automaticity over time are associated with habit formation.

Additionally, another secondary hypothesis of this trial examines the association between longitudinal behavioral automaticity and habit formation over time. These analyses will provide preliminary estimates of how behavioral automaticity changes at a given week impact the attainment of the first operationalization of habit formation, thus informing how the timing of behavioral automaticity change will impact habit. Briefly, the association between habit formation and behavioral automaticity (measured by the SRBAI) at a given week will be assessed first using univariate logistic regression. Then, weekly behavioral automaticity changes will be jointly explored in a multivariable isotonic regression model, which will be analyzed using the R package *McMiso* [85,86]. Briefly, each participant’s achievement of habit formation (binary yes or no) at a given week will be regressed on SRBAI in that week and the week number using multivariable isotonic regression. This analysis will include data up to the first week where a habit is formed; if a habit is not formed, we will use SRBAI data in all 10 weeks. To further assess lagged effects, we will next regress achievement of habit formation on SRBAI in the same week and in the previous week, as well as the week number. A few methodological notes are in order. First, these analyses will include data up to the first week where a habit is formed. For example, if a habit is not formed in a participant, we will use SRBAI data for all 10 weeks. Once a habit is formed, we will not use SRBAI data after the event, so that temporally the dependent outcome is preceded by the independent variables. Second, isotonic regression assumes a monotonic association between habit (dependent variable) and the independent variables (SRBAI and time). This assumption is reasonable because automaticity (as measured by the SRBAI) should increase proportionally as habit formation becomes more likely. Also, since time as a covariate indicates the *cumulative* risk of forming a habit, we also expect the association between habit and week number to be positive. Third, isotonic regression does not impose additional assumptions other than monotonicity, such as linearity as in logistic regression and additivity between covariates, and hence represents a data-driven tool to explore the relationship between habit and SRBAI.

A final secondary outcome for the trial is examining HTEs for habit formation and on changes in behavioral automaticity by conducting analyses of HTEs across participants. This will involve examining the heterogeneity in time to attaining the first operationalization of habitual hourly walking due to the BCT intervention.

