
### Sample Size Calculation

A sample of 100 participants is planned for enrollment into this remote trial. Up to 20% attrition is expected following the 2-week baseline period due to failure to meet wearable device and survey adherence requirements (n=20). An additional 25% attrition is expected after the 10-week intervention period due to participants becoming lost to follow-up, withdrawing, or other (n=20). The expected attrition throughout the intervention period is estimated as such because of the burdens caregivers experience due to the nature of their unique responsibilities, not limited to time constraints and motivation, which may produce barriers to longitudinal research participation [87]. We have attempted to design this trial to minimize barriers to participation for caregivers specifically, yet have estimated attrition similar to that in other longitudinal physical activity trials with caregivers to be conservative [88,89].

The trial still will have a sufficient sample (n=60) to provide adequate power. Assuming a null habit formation rate of 30% with a sample size of n=60, a 1-sided, one-sample binomial test at 5% significance will have about 92% power to declare the BCT intervention effective if the true habit formation rate is at 50% or above. We believe the null hypothesis for habit formation is conservative, as caregivers spend 80% of their time being sedentary.

To anticipate the variability due to the proposed total sample size of 60, we calculated the power to detect a difference between 20% habit formation (in the group of participants without increased behavioral automaticity) versus 60% habit formation (in the group of participants with increased behavioral automaticity) under different scenarios. Specifically, when 30% of the participants experience an increase in behavioral automaticity, there is 86% power to detect the difference. When 50% of the participants experience increases in behavioral automaticity, the power increases to about 89%.

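### The 2-sided Fisher test of habit against automaticity is valid but conservative at n=60, and its power is 83.5% and 85.1%, not the stated 86% and about 89%

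*Protocol article*

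**What the plan says.** The Secondary Outcomes and Analysis section of the protocol article cross-classifies habit formation (yes/no) with an increase in the SRBAI score (yes/no). For the latter, "a positive change is defined as a difference of greater than zero". The test is fixed: "A Fisher exact test (5%, 2-sided) will be used to examine whether an hourly walking habit formation will be associated with positive changes".

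The Sample Size Calculation section takes 60 analysed participants: "The trial still will have a sufficient sample (n=60) to provide adequate power". Its calculation concerns "power to detect a difference between 20% habit formation (in the group of participants without increased behavioral automaticity"), and sets this rate against an assumed 60% among those whose score rose. Two scenarios follow. For the uneven split, "when 30% of the participants experience an increase in behavioral automaticity, there is 86% power to detect the difference". For the even split, "When 50% of the participants experience increases in behavioral automaticity, the power increases to about 89" (a percentage). The section does not name the test behind these two figures. The article mentions no unconditional exact test.

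**The concern.** Fisher's test conditions on both margins of the 2x2 table. Here neither margin is set by the design, because the number who form a habit and the number whose SRBAI score rises are both observed. The conditioning is therefore not required. With 60 participants the conditional distribution is coarse, so the true error rate falls well below the nominal 5% and power falls with it.

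Two things follow. The power stated for this comparison may not belong to the test named for it. And some power may be recoverable at the same 5% limit by a different exact test. The comparison is a test of the trial's hypothesized mechanism, so readers will use the stated power to judge a null result.

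**Working it through.** **Inputs, all from the protocol article.** n=60. Habit rate 60% with increased automaticity and 20% without. Test at 5%, 2-sided. Split 18/42 (30% of 60 increased) or 30/30 (50%). In each split the group with increased automaticity comes first.

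**Reproducing the stated power.** The pooled normal approximation for two proportions is power = Φ[(0.40 − 1.96·s0)/s1], with s0 = √[p̄(1−p̄)(1/n1+1/n2)] and s1 = √[0.60·0.40/n1 + 0.20·0.80/n2].

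- 18/42: p̄ = (18×0.60 + 42×0.20)/60 = 0.32; s0 = 0.1314; s1 = 0.1309; z = 1.088; power 86.2%.
- 30/30: p̄ = 0.40; s0 = 0.1265; s1 = 0.1155; z = 1.317; power 90.6%.

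These lie within 2 points of the stated 86% and about 89%. So the stated figures are compatible with an uncorrected two-proportion test.

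**Power and size of the named test.** For each table with a habits of n1 and b habits of n2, compute the 2-sided Fisher p-value. Let R be the set of tables with p ≤ 0.05. Then

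- size = maximum over a common rate π of Σ_R Bin(a; n1, π)·Bin(b; n2, π);
- power = Σ_R Bin(a; n1, 0.60)·Bin(b; n2, 0.20).

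**Boschloo's test, ordered on the 2-sided Fisher p-value.** Keep Fisher's p as the statistic and raise the cut-off to the largest value whose size is still at most 5%. That cut-off is about 0.066 at 18/42 and 0.069 at 30/30. Both exceed 0.05, so this test rejects every table that Fisher rejects, and some more.

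| Split | Stated power | Fisher max. size | Fisher power | Boschloo max. size | Boschloo power | Gain (points) |
|---|---|---|---|---|---|---|
| 18/42 | 86% | 3.7% | 83.5% | 4.8% | 84.8% | 1.3 |
| 30/30 | about 89% | 2.7% | 85.1% | 4.7% | 89.9% | 4.9 |
| 29/31 | – | 3.9% | 86.4% | 4.7% | 89.3% | 2.9 |
| 31/29 | – | 3.9% | 89.0% | 4.7% | 90.0% | 1.0 |
| 20/40 | – | 3.7% | 85.4% | 4.9% | 86.5% | 1.2 |

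Gains are taken from unrounded powers.

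**Shortfall against the stated power.** 86 − 83.5 = 2.5 points, and 89 − 85.1 = 3.9 points.

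**Random split.** If the number with increased automaticity is Binomial(60, q), average power is 81.6% (Fisher) and 84.2% (Boschloo) at q=0.3, and 86.8% and 89.5% at q=0.5. The gain is about 2.7 points in each case.

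**One table.** 18/30 v 10/30 gives Fisher p=0.069 and Boschloo p=0.047.

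**The version matters.** Some software, scipy among it, forms the 2-sided Boschloo p-value by doubling the smaller one-sided value. At 18/42, the table 5/18 v 3/42 has Fisher p=0.045 but doubled-version p=0.053, so the doubled version does not reject where Fisher does. Its power at 18/42 is 83.6%, only 0.1 point above Fisher.

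**The case against.** The strongest reply is that the analysis section contains no error. A Fisher test at a nominal 5% keeps its error rate at or below 5%, and naming the nominal level does not claim an exact size. Conditional against unconditional exact testing is an old dispute in which many statisticians prefer Fisher. All of that stands. A reader might infer from the 2.7% to 3.9% sizes that the planned test is wrong or its 5% misreported; the article does not support that.

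A reader might also infer a general loss of about 5 points. The 4.9-point gain belongs to exactly 30/30, where Fisher is unusually conservative. One participant more or fewer in the first group brings it to 1.0 or 2.9 points, and the split is not under the sponsor's control.

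Nor does every test labelled Boschloo dominate Fisher, as 5/18 v 3/42 shows.

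Finally, the mechanism question does not rest on this table alone. The article also plans autoregressive models of continuous SRBAI change, a mixed-effects logistic model, and weekly logistic and isotonic regression, all of which use the repeated scores that the 2x2 table discards. This limits the consequence.

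What the reply leaves untouched is the mismatch between the two sections: the stated power is not the power of the test named. Quoting Fisher's own power would settle that without changing the test.

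**Conclusion.** The point holds as a minor one. The named test is valid and conservative, and its exact power is 83.5% and 85.1% where the article states 86% and about 89%. Boschloo's test ordered on the 2-sided Fisher p-value never rejects less often than Fisher, keeps size at or below 5% for any given split and so also for a random one, and comes within about 1.2 points of both stated figures.

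The figures assume 60 analysed participants, the article's 60% and 20% habit rates, and independent participants. If all 80 expected to enter the intervention were analysed, Fisher's power would be 92.3% (24/56) and 94.7% (40/40), against 93.6% and 96.5% for Boschloo, so the matter would count for less. No effect on the primary outcome follows.

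**What to change.** Before outcome data are seen, take one of two routes.

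1. In Secondary Outcomes and Analysis, replace the Fisher test by Boschloo's unconditional exact test at 5%, 2-sided, with the 2-sided Fisher p-value as ordering statistic, and say that the doubled one-sided version is not meant. In Sample Size Calculation, restate power as about 85% (30% with increased automaticity) and 90% (50%).
2. Keep the Fisher test and restate power as about 83.5% and 85%.

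In either case, name the test to which the power figures refer.

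The cost is a line or two of text. Route 1 also brings a test that some readers will not know, and a short program or a check of the software, because packages differ in how they form the 2-sided p-value. Route 2 costs nothing beyond the restated figures and leaves the power where it is.

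### The mixed logistic model ties the question of automaticity change to a time-by-automaticity interaction, which tests only whether the SRBAI effect differs by week; no named term isolates change

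*Protocol article*

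**What the plan says.** The Secondary Outcomes and Analysis section of the protocol article gives three analyses of the link between automaticity and habit.

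- **Fisher test.** "A Fisher exact test (5%, 2-sided) will be used" on a dichotomised change score, the mean SRBAI of the last two intervention weeks minus the baseline mean; "a positive change is defined as a difference of greater than zero".
- **Autoregressive model.** "we will model the association between habit and continuous changes in automaticity over time using autoregressive models of order 1".
- **Mixed model.** "a mixed-effects logistic regression will be used to assess the effects of behavioral automaticity on the development of a daily walking habit", adjusted for caregiver demographics and caregiving factors. For this model, "we will examine the fixed effects of automaticity, time, and the time-by-automaticity interaction effect". The end of that sentence, which gives the purpose, runs "the time-by-automaticity interaction effect to examine whether changes in automaticity over time are associated with habit formation".

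For the mixed model the article names no change score, no baseline SRBAI term and no split of SRBAI into person level and within-person deviation.

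**The concern.** A time-by-X term tests differential change when X is a group and the repeated measure is the outcome. Here automaticity is the predictor and habit is the outcome, so that reading does not carry over. The interaction says whether a given SRBAI score matters more in later weeks. It does not say whether a person whose SRBAI rises becomes more likely to form the habit.

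Automaticity is the trial's hypothesised mechanism, and this is its only automaticity model with stated adjustment for caregiver factors. A null interaction could be reported as no effect of automaticity change when there is one. A significant interaction could be reported as support for the mechanism when nobody's automaticity had to change to produce it.

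**Working it through.** **Inputs from the protocol.** Fixed effects: automaticity A, time t, and A×t. Ten intervention weeks of SRBAI. Analysed sample: "The trial still will have a sufficient sample (n=60) to provide adequate power". Planned contrast: "20% habit formation (in the group of participants without increased behavioral automaticity) versus 60% habit formation" in those with an increase.

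**Stated figures first.** No power is given for the mixed model. The nearest figures are 86% and about 89% for 20% versus 60%. The pooled normal approximation, two-sided 5%, is Φ{(0.40 − 1.96·SE0)/SE1}.

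- 42 versus 18: pooled rate (8.4+10.8)/60 = 0.32; SE0 = 0.1314, SE1 = 0.1309; power 86.2%.
- 30 versus 30: SE0 = 0.1265, SE1 = 0.1155; power 90.6%.

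Both are within 2 points of the stated figures. Exact two-sided Fisher gives 83.5% and 85.1%.

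**Algebra (no assumptions about the data).** With logit P = b0 + b1·A + b2·t + b3·A·t:

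- The log-odds per SRBAI point at week t is b1 + b3·t, so b3 is the weekly drift in that slope.
- If b3 = 0, a rise of d points still shifts the log-odds by b1·d. For example, b1 = 1.0 and d = 1 gives an odds ratio of e^1.0 = 2.72 with a null interaction.
- Write A = B + C (baseline level plus change). Then b1·A = b1·B + b1·C, which forces one coefficient on both parts. Likewise b3·A·t = b3·B·t + b3·C·t, so a stable level whose weight varies by week loads on b3.

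**Simulation 1.** n=60, 10 weeks, random-intercept logistic model, likelihood-ratio tests, 200 runs per scenario. Assumed: baseline SD 0.5 or 1.0, slope SD 0.15 per week, weekly noise SD 0.4, log-odds 1.0 per point. Rejection at 5%, as the range over the two baseline SDs:

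| Truth | Rows | A×t | A and A×t jointly | A, no interaction | Change from baseline |
|---|---|---|---|---|---|
| Constant effect of change | weekly, repeated | 9-20% | 100% | 100% | 100% |
| Constant effect of change | to first habit | 10-15% | 73-87% | 77-92% | 99% |
| Constant effect of current SRBAI | weekly, repeated | 4-6% | 100% | 100% | 100% |
| Constant effect of current SRBAI | to first habit | 4-6% | 99-100% | 100% | 94-97% |
| No SRBAI trend; slope drifts 0.25 per week | weekly, repeated | 98-100% | 96-100% | 3-4% | 4-6% |
| No SRBAI trend; slope drifts 0.25 per week | to first habit | 62-90% | 69-96% | 34-69% | 16-18% |
| No effect | both | 5-8% | 6-9% | 6-7% | 5-6% |

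Monte Carlo error near 20% is √(0.2×0.8/200) = 2.8 points.

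**Simulation 2.** 1,000 trials, rows to first habit, about 55% forming a habit. Assumed: between-person SD 1.2, noise 0.5, slope 0.10 (SD 0.15-0.20) per week, log-odds 0.8-1.2 per point of change.

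- A×t is significant in 17-23% and a change term in 83-99.7%. A change-by-week interaction reaches only 11-12%, so putting change scores into the interaction does not cure the problem.
- With no effect of change but a baseline weight that grows by week, A×t rejects in 33% and the change term in 4%.
- With repeated weekly outcomes (robust GEE), A×t reaches 23-50% and the change term 91-100%.

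Two further runs of a similar set-up gave A×t 19-22% under a change effect and 4-7% under a current-level effect. The joint test gave 68% and 85% (log-odds 0.8 and 1.2), and a change term 93-99%.

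**Simulation 3.** One habit outcome per person, GEE, 400 runs. With the protocol's 20% versus 60% by change, A×t rejects in 4-18% and Fisher in 77-89%. With only baseline level driving habit, A×t rejects in 32-73% and Fisher in 4%.

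**The case against.** The strongest reply is grammatical. The purpose clause can attach to all three fixed effects, and no sentence makes the interaction the sole test. **This stands.** On that reading, a joint test of automaticity and its interaction recovers about 68-100% power. A reader might infer that the model as specified will usually report no effect of automaticity. The documents support that only if the interaction is read alone.

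A reader might also infer that the automaticity main effect in this model is useless. One simulation has it significant in only 4-5% of trials, but that rests on two things the protocol does not state: week counted from 1 without centring, and habit depending on change alone, with baseline level having no effect. If current SRBAI drives habit instead, the same uncentred main effect rejects in 54% and 81% (log-odds 0.8 and 1.2).

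Third, change is tested elsewhere: by Fisher on a change score, by the autoregressive model, and with weekly and lagged models alongside. **This also stands**, and it limits the stakes. It would be wrong to infer that the mechanism hypothesis as a whole goes untested.

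Fourth, coding and centring belong to an analysis plan that is not shown. That is fair for the coding. But the article itself names the terms and says what they are for, and a plan that follows it inherits the mismatch.

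What survives every reading is that raw SRBAI forces one coefficient on stable level and on change, so even a joint test does not isolate change.

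**Conclusion.** The point holds in a limited form. The interaction to which the article most directly ties the change question measures week-to-week drift in the SRBAI effect. That follows from the algebra alone.

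Its size rests on assumed SRBAI variances, slopes and effects. With weekly rows to first habit at n=60, the interaction alone detects a constant effect in roughly 4-23% of trials; repeated weekly outcomes gave 9-20% in one simulation and 23-50% in another. It rejects in 33% to 100% of trials when only the weight of SRBAI drifts by week.

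The consequence is confined to one supporting secondary model. The primary outcome and the Fisher and autoregressive analyses are untouched.

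**What to change.** In the Secondary Outcomes and Analysis section, state that the tested term of the mixed model is SRBAI change from baseline (current week minus the mean of the baseline surveys), with baseline SRBAI and week as covariates beside the planned caregiver adjustments. Within-person-centred SRBAI plus the person mean serves the same purpose. Keep the interaction, with week centred, as a separate secondary test of whether the automaticity effect varies by week.

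No new data are needed. SRBAI is collected weekly in both periods, at least one baseline survey is required to enter the intervention, and the Fisher test already uses a change from the baseline mean. The cost is that the timing question, which the trial does pose, moves to a secondary check within this model; the weekly and lagged analyses still address it.

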### Baseline Period

On the participant’s assigned start date, they will begin a 2-week baseline period to assess adherence to the study protocol and preintervention behavioral automaticity. Participants will not receive any BCTs during the baseline period. Instead, they will engage in their usual level of activity, wear the Fitbit device continuously, and complete weekly SMS text message–delivered surveys via REDCap (delivered using the Automated Survey Invitations application) consisting of the 4-item Self-Report Behavioral Automaticity Index (SRBAI) [76] to assess the MoBC and a single-item assessing overall health from the EuroQol EQ-5D-5L.

To be eligible to continue into the 10-week intervention period, participants must wear their Fitbit for at least 10 hours each day for at least 12 of the 14-day baseline period and must complete one of the 2 weekly surveys. We have successfully achieved desired samples without more-than-expected baseline attrition using similar adherence thresholds used in other remotely delivered behavioral trials [77-80]. Participants who do not meet adherence requirements for the 2-week baseline period will be removed from the study. Figure 3 outlines a timeline of baseline, intervention, and postintervention digital surveys and activities for participants eligible after baseline.

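### The weekly automaticity analysis is described as being about change, but its models use the SRBAI level with no baseline term, so stable differences between caregivers could be read as an effect of change.

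*Protocol article*

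**What the plan says.** All of this is in the protocol article. Secondary Outcomes and Analysis says the weekly analyses will estimate "how behavioral automaticity changes at a given week impact the attainment of the first operationalization of habit formation". The use it names for those estimates is again about change: "thus informing how the timing of behavioral automaticity change will impact habit". Three steps follow:

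- By-week logistic: the association between habit formation and SRBAI "at a given week will be assessed first using univariate logistic regression".
- Isotonic: this step is introduced with "weekly behavioral automaticity changes will be jointly explored in a multivariable isotonic regression model". Habit status in a week "will be regressed on SRBAI in that week and the week number using multivariable isotonic regression".
- Lagged isotonic: "we will next regress achievement of habit formation on SRBAI in the same week and in the previous week, as well as the week number".

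The isotonic fit assumes a monotone relation of habit with SRBAI and with time, and the text argues that both relations should be positive.

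SRBAI is also measured before the intervention. The Baseline Period section describes two weeks of weekly surveys to "assess adherence to the study protocol and preintervention behavioral automaticity", and at least one of the two surveys must be completed to continue. Everyone who enters the intervention therefore has a baseline value. For the Fisher exact test, the secondary-outcomes section already subtracts average baseline SRBAI from the average of the last two intervention weeks.

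**The concern.** The question is about change and the covariate is a level. A weekly SRBAI value is the caregiver's starting level plus whatever change has occurred plus survey noise. With no baseline term, the models cannot tell the first part from the second.

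Two errors of interpretation become possible. A positive association can arise because caregivers who already scored high are more likely to walk consistently, with no role for change. Conversely, if change is what matters, baseline spread acts as noise and dilutes the signal.

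Automaticity is the hypothesized mechanism of behavior change and the trial has no control arm. The contrast between pre-existing level and change within a person is therefore what the weekly-timing statement rests on. This is not detail left to an unseen analysis plan, because the article itself lists the covariates of each step.

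**Working it through.** The article gives no SRBAI SD, no within-person correlation and no figure for this analysis, so there is nothing of the plan's own to reproduce. The check has three parts.

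**1. What the listed covariates can represent.** Write the weekly value as L = B + D + e, with B the baseline level, D the change and e the survey noise.
- A model in L alone gives B and D the same coefficient.
- A pure change effect is b × (L − B), which needs a coefficient of −b on B. The by-week logistic and the first isotonic model have no B.
- The lagged model holds the previous week's level and so carries some change information. A pure week-to-week change effect, however, needs a decreasing relation with the previous week's value. If the fit is constrained to be non-decreasing in each SRBAI term, as the article's rationale implies, it cannot represent that.
- A model in L and B is algebraically the same as one in change and B, so adding B to the logistic model is enough.

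**2. By-week logistic step, simulated.** From the article: n = 60 (Sample Size Calculation). Assumed: change SD 1.0, survey noise SD 0.6, habit rate about 50%, baseline taken as the mean of two surveys, weekly value one survey. When only baseline matters, the log-odds are 0.5 per point. When only change matters, they are 0.8 per point.

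| Baseline SD | Only baseline matters: level model p<0.05 | Only change matters: power, level model | Only change matters: power, change score |
|---|---|---|---|
| 0.3-0.5 | about 6-9% | 60-65% | 62-64% |
| 1.0 | 22% | 44% | about 62-63% |
| 1.5 | 56% | 31% | about 62-63% |

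With baseline SRBAI added to the level model, the false-positive rate is 5-8% across these settings, and power is equal to or above that of the level model at each.

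A hand check agrees. The share of the variance of L due to baseline is SD²/(SD² + 1.0² + 0.6²):
- SD 0.3: 0.09/1.45 = 0.06
- SD 0.5: 0.25/1.61 = 0.16
- SD 1.0: 1.00/2.36 = 0.42
- SD 1.5: 2.25/3.61 = 0.62

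The expected test statistic is about √(60 × 0.5 × 0.5) × 0.5 × SD × √share, which is 0.14, 0.38, 1.26 and 2.29. Against ±1.96 the rejection rates are about 5%, 7%, 24% and 63%. This large-sample approximation runs somewhat high at the widest spread.

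**3. Pooled weekly model, simulated.** Assumed: 60 participants, 10 weeks, data cut at the first habit week, SRBAI a stable trait plus noise with no systematic change, habit hazard dependent on the trait only. The intraclass correlation was 0.5 or 0.7, the trait log-odds 0.5 to 1.0 per SD, and 43-46% ever formed a habit. Logistic regression with participant-clustered standard errors stood in for isotonic regression (500 runs per setting). Proportion with p<0.05:
- SRBAI level plus week number: 35-94%
- week-to-week change plus week number: 5-7%
- SRBAI level plus mean baseline plus week number: 10-27%
- current-week term of the lagged model: 13-39%

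The 10-27% shows that a two-survey baseline measures the stable trait with error, so adjustment can leave residual confounding.

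**The case against.** The strongest reply is that the opening hypothesis of this paragraph concerns longitudinal automaticity, not change, and that the paragraph ends by speaking of the relationship between habit and SRBAI. A by-week level model fits both sentences, and an association driven by differences between people is still a true association with SRBAI. That stands: the result misleads only when read through the sentences about change and its timing.

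A reader might go further and infer that the trial leaves its mechanism question unanswered. The article does not support that. The same section has a Fisher test on change from average baseline, autoregressive models of continuous change over time, and a mixed-effects logistic model with a time-by-automaticity interaction. The power calculation for automaticity also concerns participants with and without an increase. These do not supply the weekly timing, but they do address change.

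The size can fairly be contested too. Enrolment requires self-reported low physical activity or walking, and the target behavior is introduced only after baseline, so baseline spread may be small. At SD 0.3-0.5 the problem nearly disappears. Neither simulation fitted the isotonic model itself.

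A change score is also not free. With one baseline survey, which the article allows, its power at SD 0.3-0.5 is 57-58% against 60-65% for the level. Finally, the analysis is secondary, is said to give preliminary estimates, and has no bearing on the primary outcome.

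**Conclusion.** The mismatch is explicit and worth correcting, within limits. The weekly analyses are said to show how changes in automaticity and their timing affect habit, and every model listed uses the level without a baseline term. Stable differences between caregivers could therefore be read as an effect of change; it does not follow that they will be.

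In the by-week logistic set-up, the level model is significant in about 6-9% of trials (baseline SD 0.3-0.5) to 22-56% (SD 1.0-1.5) when only baseline level matters, against 5-8% with baseline SRBAI added. These figures rest on assumed SDs, slopes and habit rate, and where the trial falls in the range is unknown. For the isotonic models the direction follows from the covariates, but the size has not been measured. The primary analysis and the other automaticity analyses are unaffected.

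**What to change.** In Secondary Outcomes and Analysis:

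- **By-week logistic models:** add the participant's mean baseline SRBAI as a covariate. In the settings tried this cost no power.
- **Isotonic and lagged isotonic models:** enter same-week and previous-week SRBAI as change from the participant's mean baseline, at least as a companion to the level analysis. The number of covariates is unchanged, and a monotone relation is as plausible for change as for level. State that some power may be lost if baseline spread is small and only one baseline survey is available, and that a noisy baseline may leave residual confounding.
- **Wording:** describe any result from a model that keeps the SRBAI level alone as an association with automaticity level, not with change or its timing.

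The cost is analysis wording and a few extra model fits. The baseline surveys are already part of the trial, and the article expects data collection to run until June 2026, so the change can be made before analysis.
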